### Power

We determined the power for our primary hypothesis, which stated that the 7-day PPA at the 6-month follow-up would be higher in the experimental group than in the comparator group. In order to detect a difference of 10% in quit rates between the experimental and comparator groups, with an expected quit rate of 25% in the comparator group, the study would require, at 80% power with a two-sided *p* value of 0.05, a sample size of 326 participants. Given the budget and time limitations as well as the location (eg, a small city in a sparsely populated area, which makes recruitment a challenge), a sample size of 50 has been set by the research group as a more realistic number when taking into account the available resources. Given the sample size of 50 participants equally assigned to the groups, we calculated the smallest PPA that we could detect with power greater than 0.80. Assuming that the abstinence in the comparator group will be 25% [1-3], power analysis through online calculations [57] indicate that we will be able to detect a significant difference between the experimental and comparator groups with power greater than 0.80 if the PPA in the experimental group is 59% or higher. The percentage of 59% required to obtain statistical power is considered to be very high. At the end of the study we will re-estimate the power of the final percentage differences between groups in the effectiveness report, depending on the exact final sample size as well. Nevertheless, the sample size is considered as an a priori limitation to the study.

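### The 326 participants given as the size of the whole study is the number needed per group; the stated inputs require about 652 in total

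*Protocol article*

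**What the plan says.** The Power section takes as its hypothesis that "the 7-day PPA at the 6-month follow-up would be higher in the experimental group than in the comparator group". The effect to be found is worded as "detect a difference of 10% in quit rates between the experimental and comparator groups". The comparator rate is put at 25%, and the calculation is for 80% power at a two-sided 0.05 level. The result is given as "a sample size of 326 participants", with the study as the subject of the sentence and no mention of groups or arms.

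The next sentence explains that budget, time and location led the team to choose a sample size of 50 instead. That 50 is a total: the same section says "Given the sample size of 50 participants equally assigned to the groups", and Recruitment, Randomization, and Allocation assigns 25 to each group. The section then works out a detectable abstinence rate for 50 participants and calls the sample size an a priori limitation.

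**The concern.** As worded, 326 is the total enrolment that would give 80% power, and it is compared with a total of 50. But 326 is the figure one expects per group for 25% versus 35%. If so, a per-group number is being compared with a whole-trial number.

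Two things are at stake. The paper measures its own shortfall against a requirement half the true size, so the trial looks closer to adequate than it is. And anyone who takes the figure as the total for a later trial with the same assumptions would plan for a study with roughly even odds of detecting the effect, believing the chance to be four in five.

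**Working it through.** **Inputs.** All from the Power section: comparator rate p1 = 0.25; difference 0.10 in absolute terms, so p2 = 0.35; power 80% (z = 0.8416); two-sided 0.05 (z = 1.9600). Allocation is equal, as stated there and in Recruitment, Randomization, and Allocation. No inflation for dropout is stated in the Power section; dropouts count as smokers (Participant Retention).

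**Reproducing the stated figure.** Unpooled normal approximation, number per group:

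n = (1.9600 + 0.8416)² × [p1(1 − p1) + p2(1 − p2)] / (p2 − p1)²

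= 7.849 × (0.1875 + 0.2275) / 0.01

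= 7.849 × 0.415 / 0.01 = 325.7, rounded up to **326 per group**.

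This matches the printed figure to the unit, but as a per-group number. The total is 2 × 326 = **652**.

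**Could 326 be a total under another method?** Each variant keeps 80% power and alpha 0.05:

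| Variant | Per group | Total |
|---|---|---|
| Unpooled, two-sided | 326 | 652 |
| Arcsine, two-sided | 328 | 656 |
| Pooled, two-sided | 329 | 658 |
| Pooled with continuity correction, two-sided | 349 | 698 |
| Unpooled, one-sided | 257 | 514 |
| Pooled, one-sided | 259 | 518 |
| Pooled with continuity correction, one-sided | 279 | 558 |
| Pooled, two-sided, 25% versus 15% | 250 | 500 |

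The smallest total is 500. None is near 326.

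**Power if 326 were the total (163 per group).** Standard error of the difference = √(0.415 / 163) = 0.05046. Then 0.10 / 0.05046 − 1.960 = 0.022, and Φ(0.022) = 0.509. The pooled formula gives 0.504 and the arcsine 0.506. With 326 per group the unpooled formula returns 0.800, as it should. By the pooled formula, 163 per group has power 0.776 for a 14-point difference and 0.827 for 15 points, so 80% is reached only somewhere between the two.

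**Power of the planned 50 (25 per group) for the 10-point difference.** Standard error = √(0.415 / 25) = 0.1288. Then 0.10 / 0.1288 − 1.960 = −1.184, and Φ(−1.184) = 0.118. The pooled formula gives 0.116. Exact enumeration with a two-sided Fisher test gives 0.066.

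**Size of the shortfall.**

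- Share of the requirement: 50 / 326 = 15.3% as printed; 50 / 652 = 7.7% as corrected.
- Missing participants: 326 − 50 = 276 as printed; 652 − 50 = 602 as corrected. The printed gap is 276 / 602 = 46% of the true one.

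**The case against.** The strongest reply is that nothing in the trial depends on 326. The figure is stated only to be set aside: 50 was chosen for practical reasons, recruitment ended in May 2015, and no target, analysis or decision uses the larger number. The paper does not present 50 as adequate. The Power section calls it an a priori limitation and the Discussion calls it a threat to power. Whether 50 is 15% or 8% of the requirement, the message that the trial is badly underpowered for 10 points is the same. Since 326 matches the per-group result exactly, the calculation was probably right and two words were lost in writing. Use of the figure by a later team is also hypothetical.

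Most of this is fair, and it limits the consequence: design and conduct do not change. It does not make the sentence correct. The comparison with 50 makes a total the natural reading, and nothing elsewhere in the article corrects it. Admitting a limitation does not repair the number used to show its size. It is also fair that the trial needs 652 only if a 10-point effect is the target; but that is the target the sentence names.

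**Conclusion.** The concern holds. The stated inputs give 326 per group and 652 in total (656 to 658 by the other common two-sided formulas without continuity correction), and the article presents 326 as the total. The requirement is understated by exactly half, and the gap to the planned 50 by about 54% (276 against 602). Read as printed, the figure buys about 50% to 51% power instead of 80%. The planned 50 gives about 12% power for the 10-point difference by normal approximation and about 7% by Fisher's exact test.

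This rests on the article's own assumptions: 25% versus 35% as an absolute difference, equal allocation, two-sided 0.05, and a simple comparison of two proportions at 6 months. The planned mixed model was not used for these figures, nor, as far as the text shows, for the article's own.

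**What to change.** In the Power section, restate the requirement as 326 participants per group, 652 in total, and name the formula used. Add that the planned 50 participants give about 12% power for the same 10-point difference, so that the limitation is shown at its real size.

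The cost is a correction to one sentence plus one added sentence. The stated figure becomes less favourable. Enrolment, follow-up and analysis do not change.

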### Recruitment, Randomization, and Allocation

Recruitment will occur through referrals from the health care units in the Jyväskylä area as well as via the Web pages of Central Finland Respiratory Association, the City of Jyväskylä, Radio Jyväskylä, and Yle News. All interested participants will be screened for eligibility. The enrollment period ended in May 2015. The first 50 eligible participants will start the smoking cessation intervention, which consists of 3 weekly counseling sessions and will help them set a quit date. The rest of the eligible participants will be put on a waiting list and invited to participate in case of dropouts before the quit day/randomization time point. The first 50 participants to reach the quit day/randomization time point will then form the intention-to-treat group that will continue in the study. After the quit day/randomization, participants will be assigned to an experimental group (25 participants) and a comparator group (25 participants), and both groups will separately have 1 more counseling session on how to manage cravings. In this fourth session, the only difference in treatment between the groups is that the experimental group will have an extra 10-15 minutes of guidance on how to use the Ph.o.S app to manage cravings during the follow-up period. Both groups will be followed up for the main and secondary efficacy outcomes of interest for 6 months. The method of randomization is a set of numbers generated by online software [38]. The principal investigator will generate the allocation sequence and the study nurse will assign participants to the groups. The study nurse is blind to the allocation sequence until the third session and the principal investigator is blind to the participants and their data up to the first follow-up measure.

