### Participant Retention

To prevent missing data, an effort will be made to retain the participants in the trial for the follow-up data collection. However, participants who withdraw their consent will discontinue their participation in the study. Moreover, participants who attend less than 2 out of 3 sessions of the quit smoking intervention will be excluded from the final analysis. Participants who drop out of the trial or who are lost for follow-up are considered to be smoking. The flow of the participants is presented in Figure 1.

The strategies for monitoring and improving adherence to intervention protocols include the following:

Face-to-face adherence reminder. Study participants will be well informed during the first session about the expectations regarding study procedures before they sign the informed consent form. Moreover, a reminder about the expected participation during the follow-up measures takes place during the fourth session when they are asked about their preferred way of follow-up data collection (eg, telephone, mail, email or SMS).Providing feedback about how well subjects adhere to protocol and achieve target goals whenever possible. During the follow-up period a short SMS or email message will be sent to all participants (ie, both experimental and comparator). The follow-up messages start with an acknowledgment of the participant’s contribution to date (ie, how well they adhere to the protocol), followed by a motivational message that is individualized depending on their progress (ie, relapse or no relapse). Next, information on how to fill out the follow-up questionnaire is provided and, finally, the date of the next follow-up point is reported.Monitoring adherence to the Ph.o.S app use and intervening when adherence problems emerge. In the experimental group, adherence is monitored by recording through the data collection mechanism of the Ph.o.S app. When participants do not use the Ph.o.S app for 1 week, they are asked, via SMS or email, to verify if they use the Ph.o.S app, to check if there is a technical problem, or if they have stopped using the Ph.o.S app. If they answer that they do not use the app, then they are sent a link to a short questionnaire in order to assess the reasons for discontinuing use of the app. Participants are considered dropouts when they do not respond to the invitation emails for measurement but not when they stop using the app.

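### The 59% detectable abstinence rate does not have 80% power at the stated two-sided 0.05; power there is about 70%, and the figure matches a one-sided calculation

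*Protocol article*

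**What the plan says.** The Power section of the protocol article contains two calculations for one primary hypothesis, namely that "the 7-day PPA at the 6-month follow-up would be higher in the experimental group than in the comparator group".

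- The first concerns a 10-point difference from a 25% comparator rate, "at 80% power with a two-sided *p* value of 0.05, a sample size of 326 participants". This is the only statement of sidedness in the article.
- The second concerns the trial as run. It begins "Given the sample size of 50 participants equally assigned to the groups", again takes 25% for the comparator, and concludes that a significant difference can be detected "with power greater than 0.80 if the PPA in the experimental group is 59% or higher". It restates neither alpha nor sidedness, and its source is given only as an online calculation.

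The Recruitment, Randomization, and Allocation section confirms the group sizes: "participants will be assigned to an experimental group (25 participants) and a comparator group (25 participants". The Participant Retention section says "Participants who drop out of the trial or who are lost for follow-up are considered to be smoking", so the denominator stays at 25 per group and no inflation for dropout enters the calculation.

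**The concern.** Both calculations address the same hypothesis in the same paragraph, so a reader carries the two-sided 0.05 from the first to the second. On that reading, 34 points (59% minus 25%) with 25 per group looks too small a difference for 80% power.

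The sample size of 50 was fixed by resources, so the detectable rate is the only statement of what the trial can show. If it is too low, readers of the results will take the trial to be more sensitive than it is. The article also promises to re-estimate power in the effectiveness report, and an unnoticed one-sided setting could be carried into that re-estimate.

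**Working it through.** **Inputs.** n = 25 per group (Recruitment, Randomization, and Allocation); p1 = 0.25, p2 = 0.59, two-sided 0.05 and target power 0.80 (Power). Then d = 0.34 and the mean rate is 0.42.

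- Unpooled SE = √[(0.25×0.75 + 0.59×0.41)/25] = √[(0.1875 + 0.2419)/25] = 0.1311
- Pooled SE = √[2×0.42×0.58/25] = 0.1396

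**Step 1: reproduce the article's figure.** Pooled formula: power = Φ[(d − z × pooled SE)/unpooled SE].

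- One-sided 0.05 (z = 1.645): (0.34 − 1.645×0.1396)/0.1311 = 0.842, and Φ(0.842) = **0.800**. The smallest rate reaching 0.80 is 59.0%.
- The matching sample size is [1.645×√(2×0.42×0.58) + 0.842×√(0.1875 + 0.2419)]²/0.34² = (1.148 + 0.552)²/0.1156 = 25.0 per group.
- Arcsine, one-sided: h = 2·arcsin√0.59 − 2·arcsin√0.25 = 1.752 − 1.047 = 0.705; Φ(0.705×√12.5 − 1.645) = 0.801.

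The article's 59%, 0.80 and 25 per group all come out of a one-sided 0.05 calculation.

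**Step 2: use the stated two-sided 0.05 (z = 1.96).**

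- Pooled: (0.34 − 1.96×0.1396)/0.1311 = 0.506, and Φ = **0.694**.
- Unpooled: 0.34/0.1311 − 1.96 = 0.634, and Φ = **0.737**.
- Arcsine: Φ(0.705×√12.5 − 1.96) = **0.702**.

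**Step 3: vary the method.** The exact rows sum the binomial probabilities of every 2×2 table with p ≤ 0.05.

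| Method, two-sided 0.05, 25 per group | Power at 59% | Smallest rate with 80% power |
|---|---|---|
| Unpooled normal | 0.737 | 61.5% |
| Chi-square, exact enumeration | 0.733 | 61.9% |
| Arcsine | 0.702 | 63.3% |
| Pooled normal | 0.694 | 63.5% |
| Fisher, exact enumeration | 0.626 | about 66% |
| Continuity-corrected normal | 0.580 | 67.4% |

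The first five rows fall short of 0.80 by 6 to 17 points, and the continuity-corrected formula by 22. For 80% power at 59% the pooled formula needs (1.96×0.698 + 0.842×0.655)²/0.1156 = 31.9, so 32 per group.

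**Step 4: check the sidedness of the first calculation.** For 25% versus 35%, the unpooled formula gives (1.96 + 0.842)² × (0.1875 + 0.2275)/0.10² = 325.7 per group at two-sided 0.05, and 256.6 at one-sided 0.05. The printed 326 therefore fits a two-sided test. (The formula yields that number per group, while the article presents it as the study's sample size; that is a separate matter.) The paragraph's two calculations thus appear to use different sidedness.

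**Step 5: sensitivity to the comparator rate (an assumption, not in the article).** Randomised participants have already reached their quit day, so comparator abstinence could exceed 25%. At 35% the two-sided threshold is 72% to 74% by the normal, arcsine and chi-square methods and about 76% by Fisher. At 40% it is 76% to 78%, and about 80% by Fisher. The finding does not depend on this step.

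**The case against.** **The one-sided origin is inferred.** The article attaches the two-sided level to the 326 calculation, gives no sidedness for the 59%, and words its hypothesis directionally. The match also depends on the method: one-sided unpooled gives 57.7%, and one-sided Fisher about 62%. This stands as a caution, and the origin should be called likely, not established. It does not rescue the claim. Two-sided is the only sidedness declared, a directional hypothesis does not declare a one-sided test, and an unannounced change between two calculations would itself need correcting.

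**The practical effect is limited.** The 59% did not set the sample size. The article already calls it very high and lists the sample size as an a priori limitation. Correcting it changes no group size, endpoint or analysis, and enrolment has ended. This stands, and it bears on how much the error matters. The article also makes no explicit claim about what a null result would show, so the harm lies in how readers will use the threshold.

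**No single replacement is exact.** The planned primary analysis is a generalized linear mixed model, possibly with covariates, so two-proportion formulas only approximate its power. That is a good reason to quote a range and name the method.

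**Conclusion.** The statement is wrong as written. At two-sided 0.05 with 25 per group and 25% in the comparator, power at 59% is about 70% (63% to 74% across the usual methods, 58% with a continuity correction), not above 80%. The rate detectable with 80% power is about 64% (62% to 66% by method, 67% with a continuity correction). The detectable difference is therefore about 37 to 41 points instead of 34.

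This rests on the two-sided 0.05 applying to both calculations, on 25 analysed per group, and on a simple comparison of two proportions at 6 months. The one-sided explanation is a strong inference, but the error stands whatever produced the figure.

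**What to change.** Make one of two corrections in the Power section:

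1. Replace 59% with about 64% for a two-sided 0.05 test (about 62% by the unpooled or chi-square calculation, 66% if Fisher's exact test is used), naming the test, alpha and sidedness beside the figure; or
2. Keep 59% and state that its power at two-sided 0.05 is about 70%, with the method named.

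Do not declare the primary test one-sided to justify the existing number: the article commits to a two-sided p value, and a test should not be chosen to fit a power figure. Use the same two-sided setting in any power calculation in the effectiveness report.

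The cost is one corrected figure and a slightly less favourable power statement. Trial conduct, sample size and the planned analysis are unaffected.

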## Discussion

This trial and its findings will contribute to the evidence available to inform the development and delivery of relapse prevention on smoking cessation treatment. The primary objective of the study is to contribute to the literature calling for the development of mHealth applications that support individuals in remaining abstinent after they quit smoking. The overall implementation of the project can have an impact on participants’ motivation to initiate and adhere to physical activity. Increasing physical activity can reduce health-risk factors and improve self-esteem as well as quality of life. The use of the Ph.o.S app is not restricted to any specific place, time, situation, or quitting method and it is free to use. It can also contribute to the reduction of health care costs. In addition to the impact on public health, the project will have a significant contribution to future research on how physical activity affects cigarette cravings in real-life situations and will offer the potential to improve the understanding of the mechanisms that underlie these effects. Nevertheless, the relatively small sample size due to time and budget limitations, as well as the recruitment and engagement difficulties that are common with smokers in clinical trials [58], is a threat to the power of the trial.

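### The planned end-of-study power figure uses the observed difference in abstinence, so it largely restates the p value (a minor reporting fault)

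*Protocol article*

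**What the plan says.** The Power section of the protocol article first gives prospective calculations. The opening words "In order to detect a difference of 10% in quit rates between the experimental and comparator groups", together with a comparator quit rate of 25%, imply 25% versus 35%. The stated requirement is "at 80% power with a two-sided *p* value of 0.05, a sample size of 326 participants". Resources limit the trial to 50 participants, 25 per arm, and for that size the section claims a significant difference is detectable "with power greater than 0.80 if the PPA in the experimental group is 59% or higher". It calls that rate very high and records the sample size as a limitation known in advance.

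It then adds a step for after the trial: "At the end of the study we will re-estimate the power of the final percentage differences between groups in the effectiveness report", continuing "depending on the exact final sample size as well". Two quantities therefore enter the later calculation: the difference actually seen between the groups, and the number actually available. The section does not say what conclusion would be drawn from the result. Statistical Methods bases the primary comparison, abstinence at the 6-month point (t8), on a generalized linear mixed model with possible covariates.

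**The concern.** Power describes a design: the chance of a significant result if a named true difference holds. If the observed difference is put in place of the named one, the answer depends on the same data, through almost the same statistic, as the p value. It carries no further evidence about whether the trial was large enough.

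This matters more than usual here because a non-significant result is likely unless the effect is very large. A low observed power printed beside such a result could be taken as independent support for a view that the trial was merely too small. An app with no effect would typically produce a figure just as low.

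**Working it through.** **Inputs.** From the Power section: two-sided 0.05, 25% in the comparator group, a 10-point difference, and 25 per arm. The 6/25 comparator count below is illustrative, chosen as the nearest count to 25%.

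**The plan's own figures.** These do not reproduce as stated.
- With 25 per arm and 25% versus 59%, the pooled rate is 0.42. The null standard error is sqrt(0.42 × 0.58 × 2/25) = 0.1396. The alternative standard error is sqrt((0.25 × 0.75 + 0.59 × 0.41)/25) = 0.1311.
- Two-sided power is Φ((0.34 − 1.96 × 0.1396)/0.1311) = 0.69. Replacing 1.96 by 1.645 (one-sided) gives 0.80.
- The 326 is matched as a number per arm: 0.415 × (1.96 + 0.842)² / 0.10² ≈ 326.

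That is a separate matter. The present point does not rest on either figure.

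**Observed power as a function of p.** For a z test, observed power = Φ(z − 1.96) + Φ(−z − 1.96), where z is the value that corresponds to the two-sided p.

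| p | observed power |
|---|---|
| 0.01 | 0.73 |
| 0.05 | 0.50 |
| 0.10 | 0.38 |
| 0.20 | 0.25 |
| 0.50 | 0.10 |

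**Two proportions, 25 per arm, comparator 6/25.** Here p comes from the pooled z test and power = Φ((d − 1.96 × SE0)/SE1) at the observed rates.

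| App group | difference (points) | p | observed power |
|---|---|---|---|
| 8/25 | 8 | 0.53 | 0.09 |
| 9/25 | 12 | 0.35 | 0.15 |
| 10/25 | 16 | 0.23 | 0.22 |
| 12/25 | 24 | 0.08 | 0.42 |
| 13/25 | 28 | 0.04 | 0.53 |

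The last column rises as p falls. It passes 0.50 exactly where d = 1.96 × SE0, which is the border of significance.

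**What an interval shows instead.** For 9/25 against 6/25, d = 0.12 and SE = sqrt((0.24 × 0.76 + 0.36 × 0.64)/25) = 0.1285. The 95% Wald interval is 0.12 ± 1.96 × 0.1285, or −13 to +37 points (Newcombe: −13 to +35). At 25% versus 35% the half-width is 1.96 × sqrt(0.415/25) = 25 points.

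**Power that can properly be restated.** At 25% versus 35% with 25 per arm: Φ((0.10 − 1.96 × 0.1296)/0.1288) = 0.116. With 22, 20 or 18 per arm it is 0.107, 0.101 or 0.095.

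**The case against.** Five arguments can be made for the plan.

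- **The sentence also updates for the achieved sample size.** That is legitimate when done at a prespecified difference. Here the wording names the final percentage differences as the effect, so the update does not rescue the step.
- **The identity with the p value is not exact in this trial.** This stands. The p value will come from a mixed model that may include covariates, and the power probably from an online calculator like the one used for planning. The figure would then follow the model's p value closely without being a strict function of it. The ceiling of about 50% also assumes a two-sided calculation, as the section states. A one-sided tool would give Φ(1.96 − 1.645) = 0.62 at a two-sided p of 0.05. Either way the figure carries essentially what p already conveys.
- **No misuse is planned.** This stands. A reader might infer that observed power is the plan's chosen way of interpreting a null result, or that it shields the hypothesis whatever the data show. The article contains no such rule.
- **The low-power caveat exists without this step.** This stands. A reader might take the Discussion's remark that the small sample, with recruitment and engagement difficulties, "is a threat to the power of the trial" as a second instance of the fault. It is not one: it is a fair prospective caveat and says nothing about recalculating power from results.
- **An interval may not settle the question either.** This is partly right. With a half-width of 25 points, excluding a 10-point benefit would need an observed difference near 10 − 25 = −15 points. But the interval shows that uncertainty openly, which observed power does not. Nor is the article's silence on intervals a fault, since such detail is commonly left to the full protocol or analysis plan.

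**Conclusion.** The point holds as a minor fault of reporting and interpretation. The plan commits to a calculation that is uninformative by construction: with a two-sided calculation, every non-significant result will show power of about 50% or less, whether or not the app works. The relation is exact for a z test and approximate for the planned mixed model. The conclusion rests on reading the final percentage differences as the observed ones, which is the plain sense of the words.

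Nothing in randomization, data collection, the endpoint or the primary test is affected, and no estimate is biased. It would also go too far to treat 10 points as a declared difference of interest against which the result must be judged. The article uses it as an input to the sample-size calculation and does not say more.

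**What to change.** 1. Delete the sentence that re-estimates power at the final observed difference.
2. State that the effectiveness report will give the between-group difference in 7-day point prevalence abstinence at t8 with its 95% confidence interval, obtained in a way consistent with the primary analysis.
3. If power is restated, compute it only at the prespecified 25% versus 35% with the achieved sample size, and label it so.

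The cost is one sentence in the plan and one interval in the report. Design, data collection and the primary model stay as they are. The article describes the effectiveness report as still to come and follow-up as still running, so on its own account the change could be made before reporting.
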